### **DiLCoS Substudy**

The intervention substudy is designed as a single-arm, cohort-based proof-of-feasibility study and is part of the larger BALCoS study. The study team developed the material in six stages.

- Stage 1: The latest publications, evidence-based methods and techniques, and available information regarding a module (for description of modules see Point 3.3; Study Procedures) was consulted, selected, filtered and condensed into module scripts. These scripts outlined all elements of a module (introduction, exercises, psychoeducational content, conclusionary statement) and all members of the interdisciplinary study team were asked to provide feedback. For module 2 (healthy lifestyle), a member of the nutritional counselling team at UHB was asked to review the material. For module 3 (physical activity), the physical therapy team at UHB was asked to collaborate in the development of the script. The first stage concluded with agreement on the content of the module script within the study team and where applicable the expert teams.
- Stage 2: The final scripts were reworked into standardized instructions for digital implementation. The content of the scripts was allocated to the days of the corresponding module (see Figure 2). Pictures and illustrations under the Creative Commons Zero (<https://creativecommons.org/publicdomain/zero/1.0/>) license were used to accompany the written content. The instructions were again reviewed by study team members to ensure correct implementation of the content into digital elements (recordings and edits of interviews, animated videos and audio guides).
- Stage 3: Digital elements were produced, recorded, and edited. Afterwards, they were again reviewed by the team.
- Stage 4: The finished material as well as implementation instructions were uploaded to a cloud-based storage platform for implementation into the smartphone content system

application (provided by DocDok.health; See 7.3 Overview of DocDok System).

- Stage 5: Content implemented by DocDok.health was again reviewed by the study team.
- Stage 6: Content was approved and the final version of each module was uploaded to the smartphone content system application.

### **3 PROJECT POPULATION AND STUDY PROCEDURES**

#### **3.1 Project population, inclusion and exclusion criteria**

Patients diagnosed with PCC or patients who subjectively attribute their symptoms to PCC will be included. For inclusion, signed informed consent is required. Following WHO guidelines, PCC will be defined as:

- History of confirmed or suspected SARS CoV-2 infection
- Symptoms usually start within 3 months from the onset of acute SARS CoV-2 infection with symptoms and effects that last for at least 2 months
- Symptoms cannot be explained by an alternative diagnosis

Exclusion criteria will be:

- Age <18 years
- Lack of consent to participate in the study
- Language barriers (lack of sufficient knowledge of German)
- Lack of general understanding of study procedures

#### **DiLCoS Substudy**

Participants enrolled in BALCoS who have completed the baseline measurements, but not yet T1 measurements, are asked to participate in the DiLCoS substudy. Due to a decrease in PCC referrals, patients who are further progressed in BALCoS (beyond T1) will also be invited to take part in the intervention. To evaluate their participation in the intervention, they will again complete the measures described in section below (with the last measure completed within 3 months before the start of the intervention being the new BL). Their refusal of participation in DiLCoS or withdrawal of consent during participation in DiLCoS does not affect their participation in BALCoS in any manner. There is one additional inclusion criterion for the DiLCoS substudy, which is the possession of a smartphone with an operating system that is compatible with software comprising the intervention. For being included in the DiLCoS substudy, separate signed informed consent is required (see separate document).

#### **3.2 Recruitment, screening, and informed consent procedure**

Patients will be recruited at the medical outpatient clinic unit at the UHB from February 2023 on. From this ongoing recruitment, we expect to include at least N=120 patients within the first three years of BALCoS (first patient in February 2023, first patient out February 2024; last patient in March 2025, last patient out March 2026). Recruitment shall be ongoing beyond the SERI funding phase. Enrolment will be based on the inclusion criteria mentioned above and will be carried out by the study team which includes physicians and specialized study nurses. Any patient fulfilling inclusion criteria and lacking exclusion criteria will be asked to participate in the study. The study investigator (or their designee) will obtain written informed consent from all study participants. The investigators will explain to each patient the nature of the study, its purpose, the procedures involved, the expected duration, the potential risks and benefits, and any discomfort it may entail. Each patient will be informed that participation in the study is voluntary and that he/she may withdraw from the study at any time and that withdrawal of consent will not affect his/her subsequent medical assistance and treatment. Patients will be compensated for visits that exceed standard care (see 3.3 Study procedures). The study will also be advertised by flyers sent to patients who have an appointment at the PCC outpatient clinic at the UHB before the scheduled appointment (see separate document).

Since a drop in patients was observed from December 2023 onwards, we will also invite patients treated for PCC in other consultations as well as patients who participated in PCC studies in the past from the German-speaking parts of Switzerland, Germany, and Austria. We will do so by sending physicians flyers and posters with a QR-code leading to the flyer for external patients (see separate documents) that advertise both BALCoS and DiLCoS and will ask them to advertise the study in their consultation. We will also advertise the study in PCC patient networks, press releases, and by posters in public buildings and spaces. Further, the study will be advertised online (e.g., via advertisements on social media, Google, and native advertisements). Texts will be slightly adjusted due to space constraints for the different advertising materials. However, every ad format will always link to the (approved) study advertisement. See separate documents for advertising material. In order to participate, they are required to have a report from a doctor stating a suspected or confirmed diagnosis of PCC or attribute their symptoms subjectively to PCC.

### DiLCoS Substudy

Recruitment for the DiLCoS substudy is connected to the recruitment for the BALCoS study. Once DiLCoS has started, recruitment will take place as long as recruitment for BALCoS is ongoing. Potential participants will firstly be presented with study information for BALCoS and secondly for DiLCoS and the study team will explain the nature, purpose, procedures involved, the expected duration, potential risks and benefits, and any discomfort it may entail for both research projects. A separate written consent for the DiLCoS substudy will be obtained. Consent and therefore participation in BALCoS is a requirement for participation in DiLCoS as outlined in section 3.1.

### 3.3 Study procedures

[figure not shown]

*Figure 1.* Study procedures. At Baseline (BL) and T3, psychometric measures will be completed via a tablet-based assessment whenever possible. Neurocognitive tests will be completed on a computer. If the duration of the BL assessment is too much of a strain for a patient to complete in one visit, a second visit on a separate day can be appointed, on which the neurocognitive test

battery and measures of physical performance will be assessed. If the respective consent was given, patients might be recontacted for additional assessments after T3. See appendix 1 for a summary table listing all project visits including relevant procedures, sampling, and timelines.

### **Detailed information on measures**

#### ***Clinical Data:***

Patients will be asked to give consent that all data from previous medical examinations that might be relevant to their PCC symptomatology as well as at intake will be included in the study. Further, they will be asked to give consent that data assessed in the study can be used to inform clinical routine care.

#### ***Blood Samples:***

In addition to blood drawn during the routine clinical assessment, blood samples for further analyses will be drawn at BL and T3. Blood samples that are shipped to consortium partners are described in Appendix 2 and in separate SOP forms. With these samples, genome and HLA typing (plasma), COVID-19 antibody profiling (serum), lipidome (serum), autoantibody epitopes (serum), and citrated plasma for coagulation analyses will be collected and investigated (please note that due to limited resources, for some parameters only specimens from a subsample of the enrolled patients will be sent and analyzed). Patients will be given the option to decline genome analyses and still participate in the study. In addition to the shipped blood samples, blood samples for local analyses at the UHB will be drawn. These blood samples are

- 3 PAXGene Blood RNA Tubes (genetic analyses; 2.5ml each)
- 1 x 7.5 ml EDTA (autoantibodies; prepare plasma aliquots à 1ml, freeze the cell pellet (DNA sequencing))
- 1 x 7.5 ml serum tube (immunology and hematology; prepare serum aliquots à 1ml, discard the clotted blood))

The total amount of blood drawn for BALCoS will be 45 ml.

Patients from external consultations will only be asked for the samples described in Appendix 2 to be drawn (until the predefined numbers of samples from a maximum of  $n=120$  patients are reached).

#### ***Neurocognitive Testing:***

*CNS Vital Signs* (CNSVS, <https://www.cnsvs.com/>) is a computerized neurocognitive test battery that was developed as a routine clinical screening instrument. It consists of seven scientifically valid and reliable neuropsychological tests that normally require an interviewer. The tests are: verbal and visual memory, finger tapping, symbol digit coding, the Stroop Test, a test of shifting attention, and the continuous performance test. Completion of the tests takes 40-50 minutes. The psychometric properties of the CNSVS tests have been shown to be comparable to the interview-based conventional neuropsychological tests from which they are derived (Gualtieri & Johnson, 2006).

#### ***Psychometric questionnaires:***

The *World Health Organization Disability Assessment Schedule (WHODAS 2.0)* assesses and classifies disability due to health problems during the past 4 weeks. This study will utilize the 12-item version (Üstün et al., 2010). An example item would be “In the past 4 weeks, how much difficulty did you have in walking a long distance such as a kilometer (or equivalent)?”. Items are answered on a 5-point scale ranging from 0 = “none” to 4 = “extreme or cannot do”.

Visual analogue scales (VAS): Patients will answer 4 questions on a VAS with a rating slider ranging from 0 to 10. The questions will inquire symptom intensity (10 = it can't be worse), functional impairment (10 = can't be worse), quality of life (10 = can't be better), and work capacity (10 = full work capacity). For work capacity, patients will also indicate their current incapacity to work and highest incapacity to work in relation to PCC on a slider from 0% - 100%.

As a measure of life quality, the *EuroHIS Quality-of-Life-8* (QOL-8; Schmidt et al., 2005) will be used. This 8-item instrument assesses quality of life and perceived health during the past 4 weeks, e.g. by asking “Do you have enough energy for everyday life?”. Items are answered on a

5-point scale, with wording differing between questions (e.g., from “very dissatisfied” to “very satisfied”).

The *Somatic Symptom Disorder Questionnaire* (SSD-12; Toussaint et al., 2016) assesses psychological features of somatic disorders, e.g. catastrophizing thoughts and health anxiety, e.g. with the statement “I think that my physical symptoms are signs of a serious illness”. Items are answered on a 5-point scale ranging from 0 = “never” to 4 = “very often”.

The *Patient Health Questionnaire* (PHQ-15; Kroenke et al., 2002) assesses somatic symptom severity during the past 4 weeks. Patients are asked how impaired they felt by their symptoms, e.g. back pain. Items are answered on a 3-point scale ranging from 0 = “not bothered at all” to 2 = “bothered a lot”.

The 8-item *Patient Health Questionnaire Depression Scale* (PHQ-8; Kroenke et al., 2009) assesses the severity of depressive disorders. Patients are asked if in the past weeks, they were bothered by a problem, e.g. by having little interest or pleasure in doing things. Items are answered on a 4-point scale ranging from 0 = “not at all” to 3 = “nearly every day”.

Anxiety is assessed with the *Generalized Anxiety Disorder Questionnaire* (GAD-7; Williams, 2014). It assesses if the patient was bothered by complaints related to anxiety during the past 2 weeks, e.g. by asking about having trouble to relax. Items are answered on a 4-point Likert scale ranging from 0 = “not at all” to 3 = “nearly every day”.

The 11-item *Resilience Scale* (RS-11; Kocalevent et al., 2015) asks about general resilience towards life events, e.g. “I feel that I can handle many things at a time.”. Items are answered on a 7-point scale ranging from 1 = “strongly agree” to 7 = “strongly disagree”.

Insomnia, e.g. difficulty falling asleep, is assessed by the *Insomnia Severity Index* (ISI; Morin, 1993). Items are answered on a 5-point scale with regards to severity during the past 2 weeks, with wording differing between questions (e.g., from 0 = “very dissatisfied” to 4 = “very satisfied”).

Fatigue is assessed by the 11-item *Chalder Fatigue Scale* (Jackson, 2014), e.g. by asking “Do you have difficulty concentrating?”. Items are answered on a 4-point scale ranging from 0 = “Better than usual” to 3 = “much worse than usual”.

The *Perceived Stress Scale* (PSS; Cohen et al., 1983) investigates the experience of psychological stress in the past 4 weeks. It consists of 10 items, e.g., “In the last month, how often have you been upset because of something that happened unexpectedly?”. Items are answered on a 5-point scale ranging from 1 = “never” to 5 = “very often”.

**EMA Questions:** After each measurement point (BL, T1, T2, T3), patients will be asked to answer 8 daily EMA questions for 10 consecutive days. Questions will be completed in Redcap® with the survey link being sent at 6pm via SMS and Email. On a 10-point scale ranging from 0 = “not at all” to 9 = “severely”, Patients will answer the following questions: “Over the last 24h, how much have you been:

- bothered by feeling sad, down, or uninterested in life?
- bothered by feeling anxious or nervous?
- bothered by feeling stressed?
- bothered by feeling angry?
- bothered by not having the social support you feel you need?
- bothered by difficulties to pursue your daily activities?
- fully in the moment, accepting it as it is?
- high in self-compassion towards yourself?

The *System Usability Scale* (SUS; Brooke, 1996) will be administered at T1 after completing the DiLCoS intervention. The SUS assesses how easy it is to use the system, in this case the application. It consists of 10 items, e.g. “I think I would like to use the system often”. Items are answered on a 5-point scale ranging from 1 = “strongly disagree” to 5 = “strongly agree”.

### **Measures of physical performance:**

To measure physical performance, the JAMAR® grip strength test, the 6-minute walking test, and the one minute sit to stand test will be conducted.

Grip strength will be assessed using the JAMAR®, a hydraulic grip strength measuring device (American Society for Surgery of the Hand, 1983). While sitting on a chair, the patient is instructed to squeeze the JAMAR® with one hand, while the other arm is resting in their lap. The test is repeated thrice for each hand, first for the dominant hand, then for the non-dominant hand. The best value (in kg) for each hand is taken. Further, injuries to one hand or both are noted.

The aim of the 6-minute walking test (Butland et al., 1982) is to assess functional exercise capacity by measuring the distance (in meters total) that a patient can walk in 6 minutes. Pulse and oxygen saturation is assessed at baseline, directly after finishing the test, and 2 minutes after finishing the test. Well-being before and after the test is assessed on a 5-point Likert-scale ranging from 1 = “very bad” to 5 = “very good”. After the test, perceived exertion of breathing and legs is assessed with the Borg Category-Ratio (CR) 10 Scale ranging from 0 = “no exertion” to 10 = “maximal exertion” (Borg, 1998).

The one minute sit-to-stand test (STS-60; Koufaki et al., 2002) is a measure for muscular endurance. It assesses the number of sit-to-stand cycles that can be achieved within one minute. The patient is seated on a chair without armrests and to stand up and sit continuously for one minute, without using their hands as support. The number of sit-to-stand cycles as well as oxygen saturation after completing the test is assessed.

### **DiLCoS Substudy**

The DiLCoS substudy usually starts after participants have completed the baseline (T0) measurements of the BALCoS study and before the T1 measurements. This timing ensures that the impact of the digital intervention can be isolated and accurately assessed within the broader scope of BALCoS. Due to a decrease in PCC referrals, patients who are further progressed in BALCoS (beyond T1) will also be invited to take part in the intervention. To evaluate their participation in the intervention, they will again complete the measures described in section above (with the last measure completed within 3 months before the start of the intervention being the new BL). As part of the onboarding process, participants will receive a text message sent from the DocDok system (see 7.3. Overview of the DocDok system) inviting them to install the docdok smartphone application from the Google Play Store or the iOS App Store. Included in this text message is an initial password for logging into the docdok smartphone application. Only with this password which is generated after patients are added to the study, patients can access the content of the application. After initial login, participants choose their own password and login with their personalized password from that moment. The smartphone application is equipped with a standard password renewal function, that allows participants to change their password if they have forgotten it. The study personnel facilitating the onboarding process will explain the structure of the digital intervention by going through a demonstration module together with the participant and answering questions/addressing concerns raised by the participant. The demonstration module contains a summary of the type of content that patients will receive during the intervention and a description of the structure of each module. Additionally, the module contains the remark that the primary aim of the smartphone application is clinical research. Patients are also reminded that they should contact the study personnel whenever they feel uncomfortable with an exercise and that they can skip or stop exercises at any point of the intervention. After completion of said demonstration, the participant and the study team will decide an appropriate starting date, with possible start days to be either Thursday or Friday.

DiLCoS is a 12-week program with an estimated daily time commitment of approximately 15 minutes. The intervention material is organized in 11 modules with a duration of seven days each. All 11 modules start with an introduction and a short meditation as a starting ritual. Two of these modules are wrap-up weeks (module 4 and 8), which means that patients repeat the content of previous modules. Module 9 will be one out of three different modules chosen at study enrolment: Depending on individual symptoms, the study personnel will decide together with the patients which of these modules will be allocated to them. This ensures a personalized support. At the start of each new module, participants receive a notification. They additionally receive one daily reminders via the smartphone application to engage with the digital intervention. On days 1 – 4 of each module, participants are usually provided with psychoeducational elements (e.g., information about stress), exercises (e.g. breathing exercises), and guided reflections (e.g.,

construction of an action plan with feedback on the application). Some modules will include psychometric questionnaires, however, the score will not be computed automatically. Instead, participants will be provided material and instruction in order to do so by themselves. On days 5 and 7 of each module, usually no additional or new content is provided. Those days are rest days or provide the opportunity to repeat previous content from the current module. Encouraging the participants to repeat parts of the material enables them to gain proficiency and foster their progress in areas where they can benefit most. On day 6, standardized feedback questions are asked about the module (see case report form; CRF). These feedback questions provide insight into user perceptions of the intervention's feasibility, comprehensiveness, effectiveness, and scope (e.g., length and depth of the material). After the questions, a conclusionary statement follows. The content of module 4 and 8 is solely based on the individual participant's feedback to questions 3 and 4. This feedback mechanism furthermore promotes reflection and encourages active engagement on the side of the participant. At the beginning of the digital intervention, a four-day introduction module (with day 4 being a rest day) will be provided. Likewise, a conclusion module will be provided at the very end of the intervention. See Figure 2 for an overview on the intervention structure and module content and Appendix 3 for screenshots illustrating the layout of the smartphone application and the platform where patients are added to the study by the study personnel.

[figure not shown]

Figure 2: Overview of modules and their structure.

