## Relevance to public health

Until today, the initially described complaints of fatigue, shortness of breath, and cognitive dysfunction are still reported as the most frequent symptoms of PCC (Soriano et al., 2021). A recent modelling of the WHO estimated that around 17 million Europeans experienced PCC symptoms during the first two years of the pandemic (Wise, 2022). In a Dutch cohort study, around one in eight patients with COVID-19 experienced PCC symptoms (Ballering et al., 2022). In a Swiss cohort study that was conducted during the first year of the pandemic, even 26% of enrolled participants stated that they did not fully recover 6-8 months after being diagnosed with COVID-19 (Menges et al., 2021). A UK study reported that for PCC the mean duration of illness in a large population sample was 7.2 months (Ziauddeen et al., 2022). Almost half of the Swiss population has been tested positive for SARS-CoV-2 at least once as of October 2022 (Federal Office of Public Health, 2022), which underscores the high relevance of better understanding and treating PCC also from a Swiss perspective. In sum, PCC represents a major challenge for societies and health care systems due to high individual suffering, sickness and productivity losses, large health care utilization, as well as high direct and indirect health care costs.

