## **DiLCoS Substudy**

### ***Primary Endpoint***

The primary endpoint for DiLCoS will be the change in participants' functional capacity (T0 compared to T1), as measured by WHODAS 2.0 (12-item version; Üstün et al., 2010). This measure will provide a quantifiable assessment of the impact of the digital intervention on participants' daily functioning and disability levels.

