### **DiLCoS Substudy**

A power analysis was performed using G\*Power 3.1 (Faul et al., 2007). Assuming a power ( $1-\beta$ ) of 0.80,  $\alpha = 0.05$ , and a small to medium effect size of  $f = 0.15$  in a repeated measures, within factors ANOVA with two time points resulted in  $N=105$  participants. This estimation took a possible dropout rate of 15% into account. To have sufficient power for secondary analyses, this sample size is considered as the minimal sample size and more patients will be enrolled, if feasible during the data collection phase (first patient in March 2024, first patient out February 2025; last patient in March 2025, last patient out March 2026).

The primary analysis is a pre-post comparison of the primary and secondary endpoints (see section 2.2 Primary and secondary endpoints), with T0 as a pre-intervention measure and T1 as a post-intervention measure.

As a secondary analyses, T2 and T3 will be analyzed as follow-up measures to investigate the time-stability of intervention effects. Further, a comparative analysis (DiLCoS - treatment as usual) may be performed: Patients who participated in the BALCoS study before the initiation of the DiLCoS substudy as well as patients who agree to participate in BALCoS but do not give consent to participate in DiLCoS will be considered as a non-randomised control group. This will help in distinguishing the specific effects of the DiLCoS intervention to get a comprehensive understanding of the efficacy of the digital intervention. With these two groups, generalized mixed models will be calculated to assess both within- as well as between-patient changes.

Lastly, results from the DiLCoS substudy might serve as an additional arm to another intervention study conducted within the EU consortium (AIR-program and HUS Internet Therapy Compared to Treatment as Usual in Functional Disorders and Post Covid-19 Condition; <https://www.clinicaltrials.gov/study/NCT05212467>), using a benchmarking controlled trial approach (Malmivaara, 2015). To do so, encoded data will be transferred to the “acamedic” platform (see section 7.4 Confidentiality and coding).

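### The protocol says that timing the app between T0 and T1 isolates its impact, but the single-arm pre-post comparison measures change without identifying its cause

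*Protocol*

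**What the plan says.** Protocol section 2.3 describes the substudy as "designed as a single-arm, cohort-based proof-of-feasibility study". Section 2.2 makes the T0 to T1 change in the 12-item WHODAS 2.0 the primary endpoint and calls it "a quantifiable assessment of the impact of the digital intervention". The secondary endpoints in the same section likewise treat cognitive improvement as a result of the intervention.

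Section 3.3 goes furthest. On starting the app after the baseline measurements and before T1 it says: "This timing ensures that the impact of the digital intervention can be isolated and accurately assessed". The same paragraph describes this start as the usual one only, because "patients who are further progressed in BALCoS (beyond T1) will also be invited to take part in the intervention". For those patients the last measurement taken within 3 months before the intervention becomes the new baseline (also section 3.1).

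Section 4.1 makes the pre-post comparison the primary analysis. Among the secondary analyses, "a comparative analysis (DiLCoS - treatment as usual) may be performed". Its control group is non-randomised and combines two kinds of patient: those who took part in BALCoS before DiLCoS began, and those who join BALCoS but decline DiLCoS. Section 4.1 says that this comparison would help to distinguish the specific effects of the app. It also mentions a possible benchmarking comparison with another consortium study, again as an option.

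**The concern.** Placing an intervention between two measurements fixes when change is measured. It does not show what caused the change. DiLCoS patients seek help for a condition whose course varies, and routine care continues throughout. Section 1 cites a study in which "the mean duration of illness in a large population sample was 7.2 months", so some change over a 12-week programme without the app is plausible. Regression to the mean acts in the same direction if patients enrol when they feel worst.

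What is at stake is the conclusion the trial may draw. If the T0-T1 test is significant, sections 2.2 and 3.3 license the reading that the app produced the improvement. The comparison that could bear on that reading may never be run. If it is run, its control group raises two questions that the protocol leaves open: whether the two control sources resemble the participants, and what to do with a patient who qualifies for both groups.

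**Working it through.** **Step 1: the statements side by side.** Section 3.3 says that the timing isolates the app's impact. Section 2.3 gives one arm. Section 4.1 gives a pre-post primary analysis and assigns the task of distinguishing specific effects to the control comparison. If the timing already isolated the effect, that comparison would not be needed for this purpose. Section 3.3 also departs from its own premise, because patients beyond T1 start at other times with a re-set baseline.

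**Step 2: the stated sample size.** The inputs in section 4.1 are f = 0.15, power 0.80, α = 0.05, two time points, 15% dropout and N = 105. The T0-T1 correlation ρ is not stated, so 0.5 is assumed.

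- Noncentrality: λ = f²·N·m/(1 − ρ) = 0.0225 × 90 × 2 / 0.5 = 8.1, with 1 and 89 degrees of freedom. Power is 80.4% at N = 90 and 79.9% at N = 89.
- Dropout: 90 / 0.85 = 105.9, and 90 × 1.15 = 103.5. Both lie within about one patient of the stated 105.
- Other correlations do not fit: ρ = 0.4 gives 126 and ρ = 0.6 gives 85 after dropout.

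The stated N is therefore reproduced, as the size of a one-group test that mean change is zero. It contains no control term.

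**Step 3: the effect in units of the SD of change.** dz = 2f / √(2(1 − ρ)) = 0.30 / √1 = 0.30.

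**Step 4: how often the test rejects when the app does nothing.** Completers: 105 × 0.85 = 89.25, so 89. This is a two-sided one-sample t test at 5%, with noncentrality drift × √89. The drift values are assumed; the protocol gives no figure for WHODAS change without the app.

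| Natural improvement (SD of change) | Noncentrality | Probability of rejection |
|---|---|---|
| 0 | 0 | 5% |
| 0.10 | 0.94 | 15% |
| 0.20 | 1.89 | 46% |
| 0.30 | 2.83 | 80% |

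The last row equals the design power by construction, because the drift was set to the design effect. It shows that the test cannot tell the two apart.

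**Step 5: precision of a controlled contrast.** Assume 89 controls against 89 participants, comparing change scores. The difference detectable at 80% power is about (1.96 + 0.84) × √(2/89) = 2.80 × 0.150 = 0.42 SD of change, against 0.30 for pre-post. For a true difference of 0.30 and 90 participants, power is 30%, 44%, 52% and 60% with 30, 60, 90 and 136 controls.

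**Step 6: the control group.** Section 3.2 starts recruitment at the UHB clinic in February 2023 and then says: "Since a drop in patients was observed from December 2023 onwards, we will also invite patients treated for PCC in other consultations". It goes on to add past study participants, patient networks and online advertising. Section 4.1 dates the first DiLCoS patient to March 2024. Patients from before DiLCoS therefore probably differ from participants in recruitment source and calendar time. Decliners are concurrent but self-selected. A patient who was in BALCoS before DiLCoS began and later joins the app meets both group definitions, and no rule assigns that patient.

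**The case against.** The strongest reply is that the protocol is open about its limits. It calls the substudy single-arm, proof-of-feasibility and proof of concept, and it labels the controls non-randomised. The sentence in section 3.3 ends by referring to the wider BALCoS study, so it can be read as saying only that the app sits between two scheduled assessments. This much stands: a single arm is a legitimate design for feasibility and is not the error. But section 2.1 also names effectiveness as an aim, the primary endpoint and sample size concern function, and section 2.2 repeats the causal reading.

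A reader might infer more than the documents support:

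- *The type I error is inflated.* It is not. For its own null of zero mean change the test has its nominal size, and rejecting when patients truly changed is correct. The figures above describe misattribution under an assumed drift.
- *Patients will improve without the app.* The 7.2 months is a mean illness duration from a population sample. It gives no WHODAS change over 12 weeks in these patients.
- *The optional comparison is the only controlled one, or uses only historical controls.* The benchmarking comparison is a second option, and decliners are concurrent.
- *Controls were recruited under different eligibility rules.* Section 3.1 gives one undated set of criteria, which includes self-attributed symptoms. What widened was the recruitment sources, and the exact date is not given.
- *The comparison will be unadjusted.* The protocol plans generalized mixed models and is silent on covariates, which a statistical analysis plan may supply.

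**Conclusion.** The point holds for the causal wording and for what may be concluded from the primary analysis. Section 3.3 claims a property that the design lacks, section 2.2 carries the claim into the endpoints, and section 4.1 implicitly concedes the gap while leaving its remedy optional. A statistical analysis plan could add covariates but could not make the sentence in section 3.3 true.

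The size depends on unknown natural change. With no drift there is no excess over 5%. With drift equal to the effect the trial was sized on, an inert app would give a significant result about four times in five. These figures rest on ρ = 0.5, which approximately reproduces the stated N, on 89 completers and on the assumed drift values. That one patient could sit in both comparison groups follows from sections 3.1, 3.3 and 4.1 without any assumption about effect size.

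**What to change.** 1. In section 3.3, delete the claim that the timing isolates and accurately assesses the app's impact. In sections 2.2, 3.3 and 4.1, describe the T0-T1 result as uncontrolled change, and name feasibility (use, completion, usability) as what the single arm can establish.
2. If any effectiveness statement is kept, make the non-randomised comparison in section 4.1 a commitment instead of an option. Adjust it for T0 WHODAS, which is already collected. Report pre-DiLCoS controls and decliners separately, since recruitment sources widened after December 2023. State a rule for patients who meet both group definitions. Present the result as non-randomised evidence.

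The first change costs only wording. The second costs analysis time and needs no new outcome data, because Appendix 1 schedules WHODAS at T0, T1, T2 and T3. The price is a less favourable claim and a less precise contrast: about 0.42 SD of change detectable for an assumed 89 against 89, compared with 0.30 for pre-post. Adjustment will not remove all confounding, so the comparison supports a cautious statement only.
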